### Data analysis

The secondary data will be cleaned and organized, dropping irrelevant variables and renaming covariates for ease of reference as necessary. Essentially, variables of interest in this study are binary outcomes i.e. 1 = case/the presents of an intervention, and 0 = no case, the absence of intervention, control.

Both multivariate logistic regression and Poisson with robust standard error, or negative binomial regression depending on whether there is over dispersion (conditional variance exceeding the conditional mean) will be fitted and analyzed. Thus, **loge** {*p*1 / *(1—pi)*} = *b0* + *b1 Xi1* + *b2 Xi2* + … + *bkXik*. The Use of the multiple logistic regression model also comes with the advantage of adjusting for confounding by including the covariates in the model.

For the matching method, Ghana’s DHS data sets (2008 and 2014) will be merged. This will increase the sample size to n = 8876, and add power to the study. The merger will also eliminate the risk of lack of common support, the so-called curse of dimensionality, a common phenomenon in propensity score matching, where treated units propensity scores cannot find suitable pairs.

Descriptive data will be presented using tables, frequencies, and proportions. The data will then be analyzed distinctly, using multiple statistical models and quasi-experimental design techniques. Firstly, the student independent *t*-test will be used to test for proportions, the significance of association, and mean differences between the independent variable, and the binary outcomes of interest; antenatal care uptake, and facility delivery utilization.

Test of association set < 0.05 less of significance, between the secondary variables of interest (stillbirth, perinatal death, and neonatal mortality) and the covariates; mothers age, marital status, level of education, wealth index, region, area of residence, twin delivery, parity, and employment status will be determined by using the Rao Scot Chis-square, which has an added sensitivity advantage, while adjusting for complex survey design features (weighting, clustering and stratification).

Only covariates found to be significantly associated with the dependent or independent variables will then be included in a multiple logistic regression model and adjusted for confounding [72].

Logistics regression is considered appropriate, giving the binary status variables of interest; antenatal care up-take [yes = 1 (ANC visit ≥ 4)] and [no = 0 (ANC visit of ≤ 3]; facility delivery utilization [yes = 1 (facility delivery) and no = 0 (home delivery)], and the secondary outcome variables; stillbirth, perinatal and neonatal deaths, generated through the re-coding of the relevant variable *m14, m15, b6, b7*, and *s1015,* from the DHS data sets (Table 5).

The treatment difference will be determined through nearest-neighbor matching of treated and untreated units’ propensity scores generated ex-post, and using logistics regression while controlling for the confounding variables for precision. The 'free' policy impact will then be determined using the average treatment effect on the treated. Robustness of results will be achieved with reduced standard errors using bootstrapping replication while testing for sensitivity using a t-test of bias, and probit regression.

Of the treatment and comparison country analysis, the DID analysis will be used to determine the policy impact, using the 2008 data set of the two countries (Ghana and Kenya) as a baseline and 2014 data sets as the end line. The study is powered by the sample size calculation, originally determined by the survey design. The sample size is n = 2992/5884 (8,876) for Ghana DHS 2008/2014 data sets, and n = 6079/20,964 (27,043) for Kenya DHS 2008/2014 data sets respectively.

Clustering and stratification will be adjusted for using sample survey weighting at all stages of the analysis. This will produce unbiased treatment estimate that can be generalized to the original survey population [26, 52].

The qualitative data will be deductively analyzed using predefined themes. However, common themes that emerges from the interviews and focused discussion will be organized as sub-themes and inductively reported. The approach will be aided by NVIVO 12, through which nodes and their children will be created to categories significant statements into similarities and dissimilarities [73].

The results of the primary data will be reported using the common themes approach with word frequency count and cloud, and vivid quotations to back themes. The inclusion of qualitative data will add context and situate the discussion with explanatory power to the statistical findings [48].

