**Methods:**

This study adopts a mixed-method design to estimate the treatment effect using variables generated from historical data of Ghana and Kenya Demographic and Health Survey data sets of 2008/2014, as treatment and comparison groups respectively. As DHS uses complex design, weighting will be applied to the data sets to cater for clustering and stratification at all stages of the analysis by setting the data in STATA and prefix Stata commands with *‘svy’*. Thus, the policy impact will be determined using quasi-experimental designs; propensity score matching, and difference-in-differences methods. Prevalence, mean difference, and test of association between outcome and exposure variables will be achieved using the Rao Scot Chi-square. Confounding variables will be adjusted for using Poisson and multiple logistics regression models. Statistical results will be reported in proportions, regression coefficient, and risk ratios. This study then employs intrinsic-case study technique to explore the current operations of the ‘free’ policy in Ghana, using qualitative methods to obtain primary data from the Upper East Region of Ghana for an in-depth analysis.

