### Sample weighting

Due to the complex nature of the two-stage sampling design, which essentially produces a complex survey data sets, sample weighting will be applied across the data sets, to cater for clustering (the enumeration areas) and stratification (urban/rural area of residence) for precision. Sample weighting will be set in STATA 15 software, using variable *v021* and v022 from the data sets, as primary sampling units and strata respectively. Thereafter, all commands will prefix the svy (survey) to apply sample weighting in the analysis*.*

The choice of rural/urban area of residence allows for socio-economic variation to be incorporated into the data composition and analysis. Hence, robust standard error (Taylor Linearization and bootstrapping) approach will be used to adjust for clustering and stratification bias.

Sample probability weighting will be generated through the selection of sample weighting variable *v005* from the data sets and divided by 1000,000, to cater for the 6 decimal places, usually not reported in Demographic and Health Survey data, thus, stata command of;

*gen wgt* = *v005/100,000,* then, *svyset [pw* = *wgt], psu (v021) strata (v022) to set the DHS data.*

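### The Data analysis section names a Student t-test for the two primary outcomes, against the Rao-Scott and survey-adjusted approach stated elsewhere

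*Protocol article*

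**What the plan says.** The Outcome variables section makes antenatal care uptake (4+ visits) and facility delivery the primary outcomes. Both are binary. The Variables of interest and Exposure variables sections make the mother's insurance status, as proxy for the policy, the main exposure.

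Four statements bear on how the two are to be compared:

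- Data analysis, primary outcomes: "the student independent *t*-test will be used to test for proportions, the significance of association, and mean differences", applied to the independent variable and the two primary outcomes.
- Data analysis, next paragraph: the Rao-Scott test is assigned to associations "between the secondary variables of interest (stillbirth, perinatal death, and neonatal mortality) and the covariates". Adjustment for weighting, clustering and stratification is credited to this test only.
- Abstract, Methods: "Prevalence, mean difference, and test of association between outcome and exposure variables will be achieved using the Rao Scot Chi-square".
- Sample weighting: once the survey settings are declared, "all commands will prefix the svy (survey) to apply sample weighting in the analysis". Data analysis repeats the rule: "Clustering and stratification will be adjusted for using sample survey weighting at all stages of the analysis".

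**The concern.** Two different tests are named for one comparison. Read literally, the Data analysis section gives the design-adjusted test to the secondary outcomes and an ordinary two-sample test to the primary ones.

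A Student t-test treats births as independent and equally weighted. The data come from two-stage cluster samples with unequal weights. If the t-test is run in its ordinary form:

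- the difference in proportions describes the unweighted sample, although the plan wants results that generalize to the survey population;
- the standard error leaves out clustering, so p-values can be too small.

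The first specific objective is to determine whether the policy is significantly associated with these two outcomes. The first null hypothesis is that antenatal uptake and the policy are not associated. The bivariate p-values could therefore be reported as answers to that objective. As the text stands, an analyst could produce two different p-values for the same primary outcome, each with support in the protocol.

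**Working it through.** **The contradiction** needs no arithmetic. The abstract covers prevalence, mean difference and outcome-exposure association with Rao-Scott. Data analysis covers proportions, association and mean differences for the primary outcomes with the Student t-test. The tasks are the same and the tests differ.

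**Size, if the t-test is run in its ordinary form**

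*Inputs from the protocol.* Ghana sample sizes are 2992 (2008) and 5884 (2014), from Data source and size. The merged size reproduces the plan's own figure: 2992 + 5884 = 8876. Clusters, from Demographic and health survey data, are 412 − 1 = 411 (2008) and 427 (2014). The significance level is 0.05, from Data analysis.

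*Births per cluster, m:*

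- 2008: 2992/411 = 7.3
- 2014: 5884/427 = 13.8
- merged: 8876/838 = 10.6 (10.59 before rounding)

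*Assumptions.* The protocol gives no ICC, design effect or spread of weights, so the ICCs below are assumed. The test is taken as two-sided and clusters as equal in size. Weights and stratification are left out of this calculation.

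*Formulas.* For a two-group comparison in which the exposure may vary within clusters:

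- DEFF = 1 + (m − 1) × ICC(outcome) × ICC(exposure)
- actual type I error = 2 × [1 − Φ(1.96/√DEFF)]

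*Results, merged Ghana data, m − 1 = 9.59:*

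| ICC outcome | ICC exposure | DEFF | Type I error |
|---|---|---|---|
| any | 0 | 1 | 5.0% |
| 0.05 | 0.05 | 1 + 9.59 × 0.0025 = 1.02 | 5.3% |
| 0.1 | 0.1 | 1 + 9.59 × 0.01 = 1.10 | 6.1% |
| 0.2 | 0.2 | 1 + 9.59 × 0.04 = 1.38 | 9.6% |
| 0.3 | 0.3 | 1 + 9.59 × 0.09 = 1.86 | 15.1% |
| 0.05 | 1 | 1 + 9.59 × 0.05 = 1.48 | 10.7% |
| 0.1 | 1 | 1 + 9.59 × 0.1 = 1.96 | 16.1% |
| 0.2 | 1 | 1 + 9.59 × 0.2 = 2.92 | 25.1% |

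The last three rows are for an exposure that is constant within every cluster, which insurance status is not. For Ghana 2014 alone (m = 13.8) the formula gives 6.5%, 11.1% and 18.1% when both ICCs are 0.1, 0.2 and 0.3.

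*Check by simulation.* There were 3000 runs per setting with beta-binomial outcome and exposure, at assumed prevalences of 0.7 and 0.5. With 427 clusters of 14, the naive t-test rejected in 5.9%, 11.2% and 18.6% of runs with both ICCs at 0.1, 0.2 and 0.3. With 411 clusters of 7, it rejected in 5.9%, 7.7% and 11.2%. A cluster-linearised test stayed between about 4.3% and 6.0% in every setting run.

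**The case against.** **The plan may not intend to drop the design.** The Sample weighting section puts every command under the survey prefix, and Data analysis promises adjustment at all stages. A survey-weighted comparison of two means also yields a t statistic, so this could be loose naming in a condensed article. That stands in part: the protocol nowhere says the t-test will be unweighted, and a reader who infers that the design will certainly be ignored goes further than the text. It does not remove the contradiction with the abstract. Nor does it explain why design adjustment is credited to Rao-Scott alone, and only for the secondary outcomes.

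**The t-test is only the first step.** It opens a sequence: "The data will then be analyzed distinctly, using multiple statistical models and quasi-experimental design techniques". Logistic or Poisson regression, matching and difference-in-differences follow, and the policy effect is to come from the last two. This stands. A reader might infer that the policy-effect estimates are compromised, but nothing in this sentence reaches them.

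**The inflation may be small.** A reader might infer a false-positive rate well above 5%, even 10% to 29%. Such values arise if 2008 is contrasted with 2014, because survey year is constant within every cluster. That contrast belongs to the matching and difference-in-differences analyses. Insurance status can differ between women in the same cluster, so the inflation depends on the product of two ICCs and is slight when both are 0.1 or less. This stands too. Some clustering of the exposure is still likely. The file is a children's file and the exposure is the mother's, so siblings share it exactly, and the plan itself treats region and residence as confounders. The documents do not say how much.

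**Conclusion.** The Data analysis section is wrong as written for the primary outcomes. It names a Student t-test where the abstract names Rao-Scott, and it does not fit the plan's own survey rule.

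If an ordinary t-test is run, the estimate is not for the survey population and the type I error is about 5% to 6% when both ICCs are 0.1 or less. On the merged Ghana data it is about 10% at 0.2 and 15% at 0.3. For Ghana 2014 alone it reaches about 18% at 0.3. Higher values need an exposure constant within clusters. All of these rest on assumed ICCs, so the protocol supports saying that the error can exceed 5%, but not by how much. The point concerns the bivariate test for the first objective only.

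**What to change.** Replace the t-test sentence in Data analysis with wording such as: *The association of insurance status with antenatal care uptake (4+ visits) and with facility delivery will be described by weighted proportions and tested with the Rao-Scott chi-square (svy: tabulate). Differences in proportions will be estimated with survey-weighted regression (svy: regress, lincom) and reported with design-based confidence intervals.* This brings the section into line with the abstract and the Sample weighting section. It should be settled before the data are analysed.

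The cost is one sentence, standard commands in software the plan already uses, and somewhat wider intervals. From clustering alone, the widening over the naive interval is √DEFF. On the merged Ghana data that is √1.02 ≈ 1.01, √1.10 ≈ 1.05, √1.38 ≈ 1.18 and √1.86 ≈ 1.36 when both assumed ICCs are 0.05, 0.1, 0.2 and 0.3. Unequal weights may change this further, by an amount the protocol does not allow one to calculate.

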Essentially, the ‘free’ policy lacked an operational framework for implementation, but had a political directive that ensured that every pregnant woman gets to register with the national health insurance scheme (NHIS), without paying a premium, and then access comprehensive maternal healthcare free of charge from NHIS accredited health service providers up to 90 days post-delivery [25, 27].

The government of Ghana has since invested several millions of Ghana cedis in a bid to keep the policy running amidst NHIS reimbursement challenges. With nearly 3million women benefitting from the ‘free’ package as by 2013 [28, 29], studies are yet to report on the policy gains or otherwise relative to perinatal healthcare outcome.

Despite the huge financial investment on the free policy intervention, literature is rather restricted to reporting on a nominal increase in attendance at healthcare facilities regardless of time-variant factors and somewhat monotonously on factors that affect the implementation process. Moreover, the existing literature turns to focus more on the policy effects on mothers and less on the unborn and the newborn.

Thus far, the ‘free’ maternal health care policy relationship with maternal healthcare utilization and outcomes, vis a vis medium to long term impact on perinatal healthcare has yet to be adequately documented [30–32].

Incidentally, perinatal death is also poorly researched in Ghana and Sub-Saharan Africa despite its economic burdening abilities [11, 14]. Stillbirth which accounts for a large portion of perinatal deaths has been estimated to have dire consequences on household healthcare expenditure, particularly in areas where the ratios are considered worse than child mortality due to malaria and HIV/AIDS [33–35].

This notwithstanding, perinatal deaths continue to receive little attention in public health and policy research [36, 37]. Hence, this current study seeks to examine the ‘free’ policy effect on maternal healthcare utilization after a decade of implementation and to measures its contributions towards the reduction of stillbirth, perinatal deaths, and neonatal mortality in Ghana.

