### Statistical methods and rationale

The design and intentions of the ‘free’ policy could not allow for randomization, the gold standard for impact evaluation, hence, quasi-experimental methods; DID and PSM techniques are adopted for the analysis of the secondary data sets. These methods are considered appropriate in evaluating public health programs that have no randomization in the policy design and implementation stages, and in particular, suitable for policies whose choice of participation is somewhat open and voluntary.

Combining the two methods gives the advantage of one making up for the limitations posed by the other. The DID analysis will employ the 2008 data sets of the two countries as baseline data (the starting time), whereas the 2014 DHS data sets of the same will represent the end line (the end time), as shown in Table 2.

**Table 2 Tab2:** Difference-in-differences method

	Before treatment	After treatment	Difference
Treatment (T)	X_0_	Y_0_	T = Y_0_–X_0_
Comparison (C)	X_1_	Y_1_	C = Y_1_–X_1_
Difference	X_0_–X_1_	Y_0_–Y_1_	DD = (Y_0_–X_0_) – (Y_1_–X_1_) = T-C

The choice of propensity score matching technique is also appropriate for the estimation of the policy average treatment effect through the generation of comparators ex-post. A drawback of PSM is the risk of lack of common support for paring treated units to the untreated. This particularly occurs when the sample size is small, so-called the curse of dimensionality. However, this study will merge the 2008/2014 data sets to increase the sample size and to minimize the risk of the curse of dimensionality [49].

Increased sample size will also enhance the study power for precision, albeit, also determined in the original two-stage DHS sampling design. The combined effect of the two quasi-techniques will eliminate the limitation of one and enhance the robustness of the study results [64, 65].

From Table 2 above, before treatment (baseline) is represented be GDHS 2008 (X_0_) for the treatment, T, and KDHS 2008 (X_1_) for the comparison group, C. The after treatment (end line) is also represented by Y_0_ and Y_1_ for Ghana DHS 2014 and Kenya DHS 2014, respectively. Thus, the DID analysis is the difference of T = (y_0_–x_0_) and C = (y_1_–x_1_); estimate for the before treatment difference and the after-treatment difference. The differences between the two represent the treatment effect, thus, the treatment effect is = (y_0_–*x*_*0*_) − (y_1_–*x*_1_), which is equal to T-C.

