### Covariates

Covariates are the moderating factors identified in the study conceptual framework. Covariates that show significant association with the variables of interest under consideration will be controlled for using multiple logistic regression. These include maternal characteristics such as; age, parity, pregnancy status, cesarean section, educational status, twin pregnancy, income level, abortion, and marital status. These will be adjusted for as confounding using logistics regression models. Population characteristics such as wealth index, distance, region, educational status, and rural/urban residence will also be adjusted for as confounding variables [42].

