### Protocol implementation

This protocol will be implemented in phases as per the design. Proposal writing preceded the protocol’s approval and the approved protocol will be implemented as outlined in Table 6 (see Additional file 1). The implementation will also be monitored by the Ghana Health Service Ethics Committee, as well as the supervisory committee of the University of Ghana Public Health School. The approved protocol follows the standard of research required for the award of a doctoral degree set out by the University of Ghana.

**Table 6 Tab6:** Protocol implementation, monitoring & evaluation

Phase I	Phase II	Phase III
*Review of relevant literature on;* Maternal health care policy Maternal health care utilization Burden of stillbirths Perinatal deaths Neonatal mortality *Retrieval of secondary data from MEASURE DHS;* Ghana DHS 2008 Ghana DHS 2014 Kenya DHS 2008 and Kenya DHS 2014 *Cleaning and organization of DHS data:* Dropping of irrelevant variables Merger of data sets *Variable management* recoding and renaming *Preliminary analysis of DHS data (secondary data)* Hypothesis testing Analysis of association and Determination of significant levels (set at ≤ 0.5)	Gaining entrée for primary data collection *Primary data collection* In-depth interviews (IDIs) of service providers Focus Group Discussion (FGD) among pregnant women *Preliminary analysis of qualitative data* Data transcription Annotation of significant statement Coding and Categorization of common themes *Key Informant Interviews* Transcription of key informant interviews *Triangulation of data* Drawing congruence of policy user Perspective/perception, Service provider perspective and Policy implementers view points	*Presentation of preliminary findings and feedback at;* Institutional level Clinical forum ANC clinic to policy users *Summary presentation at;* Regional Annual Performance Review *Presentation of final report at;* School of Public Health, University of Ghana *Publication of Final report for policy actors, research and scientific community in;* MOH reports NHIA report Internal journals Local journals Policy briefs
Monitoring and evaluation of phase I, II, and III		
Guidance and comments of Co-investigator 1,2 and 3	Guidance and comments of Co-investigators 1 and 2	Scheduling of presentation Purview of Co-investigators and faculty of Health Policy Planning Management of the University of Ghana Public Health School

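### Survey round and birth year are not named as covariates for the NHIS-card regressions, so any such model fitted to the merged Ghana 2008 and 2014 rounds is open to confounding by calendar time.

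*Protocol article*

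**What the plan says.** **Exposure.** Variables of interest and Exposure variables make the mother's health insurance status the main exposure, as a proxy for the free policy. Table 5 derives it from the NHIS-card variable. Antenatal care uptake (four or more visits) and facility delivery are the primary outcomes.

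**Merged data.** Statistical methods and rationale says "this study will merge the 2008/2014 data sets to increase the sample size", in a paragraph on propensity score matching. Data analysis says that Ghana's "DHS data sets (2008 and 2014) will be merged", again for the matching, and gives the sizes as "2992/5884 (8,876) for Ghana DHS 2008/2014 data sets". Table 6 (Protocol implementation) lists "Merger of data sets" in Phase I, ahead of hypothesis testing and analysis of association. Data analysis then describes the treatment difference as obtained by nearest-neighbour matching and "using logistics regression while controlling for the confounding variables for precision".

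**Covariates.** The Covariates section lists maternal characteristics and adds: "Population characteristics such as wealth index, distance, region, educational status, and rural/urban residence will also be adjusted for as confounding variables". Data analysis lists the covariates to be screened against the secondary outcomes (mother's age, marital status, education, wealth, region, residence, twin delivery, parity, employment) and sets the entry rule: "Only covariates found to be significantly associated with the dependent or independent variables will then be included in a multiple logistic regression model". Survey round, interview year and birth year appear in neither place, and no regression is said to be run separately by round.

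**Time.** Background faults earlier literature for reporting a "nominal increase in attendance at healthcare facilities regardless of time-variant factors".

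**The concern.** Survey round is a design variable that can be related to both sides of the card model. Table 1 shows policy enrolment rising from 383,216 (2008/2009) to 774,009 (2013), and Background speaks of rising attendance. If card holders come more often from 2014, and service use was higher for everyone in 2014, a pooled model without round attributes part of the time trend to the card. The adjusted ratio for antenatal care or facility delivery could then exceed 1 and reach significance with no card effect in either round. That bears on objective 1 and the first hypothesis, and it would repeat the weakness for which the article criticises earlier work.

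The card also means different things in the two rounds. Demographic and health survey data says that births of the last five years are covered, and the policy began in July 2008, so many births in the 2008 round predate it. The same section says that the 2008 survey collected NHIS data, whereas the 2014 survey collected information on the free policy. A single pooled card coefficient hides that difference.

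**Working it through.** **The plan's own figures.** 2992 + 5884 = 8876, as stated. Enrolment ratio from Table 1: 774,009 / 383,216 = 2.02. These are enrolment counts, not card prevalence in the survey samples. The article gives no prevalence, effect size or power figure for the card model, so there is nothing further to reproduce.

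**Inputs.** Round sizes 2992 and 5884 are from Data analysis; the 0.05 level is from Data analysis and Discussions (two-sided assumed). Card prevalence by round (c0, c1), outcome prevalence by round (y0, y1) and the design effect are assumptions.

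**Method.** Set the card effect to zero within each round and add the expected 2x2 tables:

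- a (card, outcome) = 2992·c0·y0 + 5884·c1·y1
- b (card, no outcome) = 2992·c0·(1−y0) + 5884·c1·(1−y1)
- c (no card, outcome) = 2992·(1−c0)·y0 + 5884·(1−c1)·y1
- d (no card, no outcome) = 2992·(1−c0)·(1−y0) + 5884·(1−c1)·(1−y1)
- pooled OR = ad/(bc); SE of log OR = √[deff·(1/a + 1/b + 1/c + 1/d)]; z = log OR / SE
- false-positive rate = Φ(z − 1.96) + Φ(−z − 1.96)

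**Worked case.** Card 35% to 65%, outcome 75% to 85%, design effect 2:

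- a = 4036.3, b = 835.5, c = 3209.1, d = 795.1
- OR = (4036.3 × 795.1)/(835.5 × 3209.1) = 1.197
- risks 82.85% and 80.14%, a difference of 2.7 points
- log OR = 0.180, SE = 0.0776, z = 2.32, false-positive rate 64%

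**Four scenarios, design effect 2**

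| Card 2008 to 2014 | Outcome 2008 to 2014 | Pooled OR | Risk difference (points) | False-positive rate, no round term |
|---|---|---|---|---|
| 35% to 65% | 75% to 85% | 1.20 | 2.7 | 64% |
| 35% to 65% | 55% to 70% | 1.20 (1.195) | 4.1 | about 80% |
| 40% to 60% | 75% to 85% | 1.13 | 1.8 | 34% |
| 40% to 50% | 75% to 80% | 1.03 | 0.45 | 6.5% |

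A simulation of 4000 data sets per scenario agrees: 64.1%, 80.4%, 33.1% and 6.6% without a round term, against 5.2%, 5.3%, 5.5% and 4.8% when stratified by round. For the first scenario, design effects of 1.5 and 3 give 76% and 47% by the formula (75% and 49% simulated).

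**A second set of assumptions** (card 30–50% in 2008 and 50–70% in 2014; use 55–60% and 60–75%) gives pooled odds ratios from 1.02 (card 40% to 50%, use 60% to 65%) to 1.40 (card 30% to 70%, use 55% to 75%) whenever both rise. Card 40% to 60% with use 60% to 70% gives OR 1.08 and z = 1.79, not significant even with no design effect. When only one of the two rises, the pooled OR is 1.00. The round-stratified OR is 1.00 throughout.

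**The case against.** Much of the case on the other side stands.

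- **Pooling is not stated for the card regression.** The merger is tied by name to the matching method, and Data analysis says that the data will be analysed distinctly by several models. Table 6 lists the merger after all four Ghana and Kenya files, so it could equally mean building the difference-in-differences file. Pooling remains the natural reading: the merger precedes hypothesis testing, Table 5 derives the card from the 2008/2014 sets, and matching is paired with logistic regression. It is an inference all the same.
- **The lists are not closed.** Covariates uses open wording. The enumerated list in Data analysis belongs to the screen for stillbirth, perinatal and neonatal death, not to the primary outcomes. A reader might infer that time is barred from the model; the article only fails to name it. Even so, a time term added later would still have to pass the significance screen, which is the wrong rule for a design variable.
- **The policy-impact claim sits elsewhere.** Objective 1 and the first hypothesis concern association. Impact is assigned to the average treatment effect on the treated and to difference-in-differences, and the latter sets Ghana's change against Kenya's. A reader might infer that the whole evaluation credits secular trends to the policy; the article does not support that.
- **The calculations are crude.** They use assumed prevalences and no adjustment for education, wealth or residence, which may absorb part of the trend.
- **A round term cannot be used everywhere.** Study design makes round itself the treatment in the matching (2014 treated, 2008 untreated), so round cannot be adjusted for there.

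It could also be said that an article leaves model terms to a fuller plan. Here, however, the article itself fixes an entry rule and names candidate covariates, and that text needs the edit.

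**Conclusion.** The point holds conditionally. Wherever a card-exposure logistic or Poisson model is fitted to the merged Ghana rounds under the stated entry rule, calendar time is an unaddressed confounder. It biases the card association upwards if both card holding and service use rose between rounds.

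The size cannot be fixed from the document. In the four tabulated scenarios at design effect 2, the pooled odds ratio runs from about 1.03 to 1.20 and the false-positive rate from about 6%, which is negligible, to about 80%. The 64% and 80% figures illustrate what could happen; a reader should not take them as the error rate of this plan. They rest on assumed prevalences, an assumed design effect and unadjusted 2x2 tables. No calculation was made for the mortality outcomes, so no size is claimed there.

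The Ghana-Kenya difference-in-differences analysis is not affected. The amendment is worth making because it is cheap and returns the null odds ratio to 1.00 in every scenario examined.

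**What to change.** 1. In Covariates and Data analysis, name survey round, and birth year within round, as forced terms in every card-exposure logistic or Poisson regression fitted to merged Ghana data, exempt from the p < 0.05 screen.
2. Report the card effect by round, or with a card-by-round term. Within 2008 the card largely reflects ordinary NHIS membership for births before July 2008, so the round-specific estimates should be interpreted separately.
3. State which regressions use merged data. If the card models are to be run separately by round, saying so also settles the confounding between rounds.
4. Reconcile the treatment definitions. Study design makes 2014 versus 2008 the treatment in the matching, while Variables of interest and Exposure variables make the card the exposure. If the card is the treatment in a propensity model, match within round. That is impossible for the 2014-versus-2008 matching.

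**Cost.** One or two sentences and one or two model terms. Round is known for every record, and birth history is among the items that the article says were collected. Expect a small loss of precision and probably a smaller card effect. The change does not remove self-selection into card holding, which should be acknowledged.
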